## **SUBJECT SELECTION CRITERIA**

### **Subject recruitment**

Patients admitted with a diagnosis of spontaneous aSAH will be assessed by the study team against the inclusion and exclusion criteria. Identified subjects who fulfil the criteria will be approached by a designated medical member of the study team, who will in turn obtain consent according to the informed consent procedure (see section 0 INFORMED CONSENT).

### **Inclusion criteria**

1. Austria: Informed consent is obtained from patients with capacity. If patients lack capacity, informed consent is obtained from a personal legal representative. If no suitable personal legal representative is available and the treatment needs to be given urgently, written informed consent will be obtained as soon as the participant is responsive or a representative is available.
- Germany: An independent physician is to be consulted to confirm that the presumed will of the patient on the participation in the study has been determined and respected. Written informed consent will be obtained as soon as the participant regains capacity.
2. Male or female patients aged 18 to 75 years (inclusive).
3. World Federation of Neurological Surgeons (WFNS) grade III-IV.
4. Ruptured saccular aneurysm, confirmed by angiography.
5. Onset of aSAH clinical symptoms within the preceding 48 hours.
6. Treatment of aneurysm via surgical clip ligation within 72 hours of aSAH is achievable.
7. Female patients of child-bearing potential must have a negative pregnancy test (urine or serum) at screening and must agree to use adequate birth control up to 12 weeks after implantation of the study drug. Female patients are considered to be not of child-bearing potential if they have a history of tubal ligation or hysterectomy or are post-menopausal with a minimum of 2 years without a natural menstrual cycle. Male

patients must agree to use adequate birth control up to 12 weeks after implantation of the study drug.

#### **Exclusion criteria**

1. SAH due to other causes (e.g. trauma, fusiform or mycotic aneurysm).
2. World Federation of Neurosurgery (WFNS) grade I, II and V patients.
3. Pregnant or Lactating Women.
4. Intraventricular or intracerebral blood, in the absence of subarachnoid blood.
5. Treatment of aneurysm via endovascular embolisation.
6. Presence of moderate or severe vasospasm on screening angiography.
7. Any known or CT /MRI evidence of previous major cerebral damage
8. Evidence of a cerebral infarction with neurological deficit on pre-treatment CT/MRI.
9. History of malignant disease (except for non-melanoma skin cancer) within the previous 5 years or any history of malignant brain tumours or brain metastasis.
10. Patients who have received an investigational product or participated in another interventional clinical study within 30 days prior to randomisation.
11. Patients with known allergy for Poly(D,L-lactide-co-glycolide) (PLGA) or nicardipine.
12. Major complication during aneurysm repair such as, but not limited to, massive intraoperative haemorrhage, brain swelling, or inability to secure the ruptured aneurysm.

#### **Subject withdrawals**

In all circumstances, patients and/or personal legal representatives should be made aware of the rights to refuse participation in a clinical trial and are entitled to freely withdraw their informed consent, without giving reasons. Patients and/or personal legal representatives should be assured that the withdrawal from the trial will not cause prejudice, will not result in any determinant and will not affect treatment. In addition, refusal to give consent or withdrawal of consent to participate in research must not lead to any liability or discrimination (e.g., with regard to insurance or employment) against the person concerned.

The Investigator also has the right to withdraw subjects from the study in the event of:

- Use of any concomitant medication specified as not permitted
- Noncompliance with the protocol and/or lack of willingness or commitment to co-operate in all phases of the study
- Protocol deviations
- Pregnancy after entry into study
- Adverse event which is considered intolerable by the patient and/or legal representative

471 • Intercurrent illness that necessitates pharmacological treatment with a drug which  
472 interacts in any way with the test treatment

473 • Development of an exclusion criterion

474 Should a patient and/or personal legal representative decide to withdraw for other reasons, all  
475 efforts will be made to complete and report the observations as thoroughly as possible. A  
476 complete final evaluation at the time of withdrawal will be performed with an explanation of  
477 the exact reason why the subject is withdrawing from the study.

478 The Investigator is responsible for the optimal individual treatment of the patient.

479 The Investigator must fill in the “Study termination” in the case reporting form (CRF)  
480 explaining all reasons for withdrawal.

481 After a patient withdraws from the trial, the Investigator is still responsible for reporting  
482 SAEs considered causally related to the study drug as well as any pregnancy and outcome of  
483 the pregnancy. In addition, the Investigator needs to ensure appropriate treatment and follow-  
484 up of each adverse event still ongoing at the time of the patient’s discontinuation.

485 No reproductive toxicology or embryo/foetal development studies have been performed with  
486 NicaPlant®. The product will not be used in pregnant women.

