143 NicaPlant® up to patient discharge, or day 21, whichever occurs first.

144 Clinical Outcomes will be recorded at 12 weeks and 1 year (week 52) after the aSAH.

145 A data safety monitoring board (DSMB) will be set-up to monitor safety throughout the trial  
146 period and provide recommendations for any necessary actions. A steering committee will  
147 receive and review the reports from the DSMB and take action as appropriate.

The final analysis will be carried out when the final patient completes the week 12 assessment. Data collected for patients at Week 52 after aSAH will be analysed and included as an addendum to the final report.

Given that NicaPlant® is implanted at the time of aneurysmal clipping, it should be emphasised that the investigational product cannot be withdrawn after implantation.

In summary, published data on the safety and effectiveness of NPRIs supports the premise that NicaPlant® offers significant potential therapeutic benefits, without significant clinical risk.

Furthermore, the results of the phase IIa study involving a total of 10 actively treated patients (with 2 patients each in 3 and 6 Implant groups and 3 patients each in 10 and 13 Implant groups) demonstrate that NicaPlant® was safe and well-tolerated up to 13 implants/ patient.

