1031       AEs occurring after day 21±1 will be collected but will no longer be considered treatment  
1032       emergent.

1033       **Reporting serious adverse events to the sponsor**

1034       All SAEs must be reported to NeuroScios PV within 24 hours of awareness, regardless of  
1035       causal relationship. For SAE reporting, the part 11 CFR compliant safety database Aquila  
1036       CTPV provided by NeuroScios GmbH will be used. For each trial site investigators will be  
1037       provided with an access to the database on a dedicated server. SAEs will be signed  
1038       electronically by the investigator within the database and will be automatically distributed to  
1039       PV, sponsor representative(s), the project manager and the investigator as confirmation of  
1040       receipt. Sponsor medical monitor/medical advisor is responsible for expectedness evaluation  
1041       of the reported event.

1042       Each SAE form must be printed by a member of the PV team and retained in the TMF in  
1043       paper form. MedDRA coding of events will be performed by PV Unit within Aquila CTPV.

1044       All SAEs occurring until 30 days after study end of each patient must be reported to by the  
1045       Investigator or designated assistant is made aware of the event and by full report as soon as  
1046       possible thereafter.

1047       In case of system failure of Aquila, all SAEs must be completed in the corresponding paper  
1048       version in the investigator site file (ISF) and emailed to: [[contact]](mailto:[contact]) within  
1049       24 hours after knowledge of the event.

1050

1051       Pregnancies occurring during the study must be reported immediately by fax or email using  
1052       the Pregnancy Report Form.

1053       In case that an event is both serious and unexpected and a reasonable causal relationship to  
1054       IMP administration is given, it constitutes a suspected unexpected serious adverse reaction.  
1055       PV will report any SUSARs occurring in the trial to the relevant CAs, Ethics Committees  
1056       (EC(s)), all study PIs and the DSMB as outlined in section 0.

1057       NeuroScios will keep the Investigator and DSMB (section 0) informed of all SUSARs  
1058       reported to them for the product under investigation, from anywhere in the world, for the  
1059       duration of the trial at a frequency appropriate to the trial.

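### The investigator may withdraw a patient from the study after surgery for any protocol deviation or similar ground, which ends no exposure but can end collection of outcomes still due

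*Protocol*

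**What the plan says.** **Right to withdraw.** Protocol section 4, Subject withdrawals: "The Investigator also has the right to withdraw subjects from the study in the event of" a list of circumstances. Four of them are for the investigator to determine:
- use of a non-permitted concomitant medication;
- protocol deviations, with no word such as major or safety-related attached;
- "Intercurrent illness that necessitates pharmacological treatment with a drug which" has any interaction with the test treatment;
- development of an exclusion criterion.

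The text does not separate the time before surgery from the time after it. The withdrawal is from the study, and a study termination page is completed in the CRF.

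**Retention of data.** The sentence promising every effort to complete the observations begins: "Should a patient and/or personal legal representative decide to withdraw for other reasons, all". It is followed by a provision that a "complete final evaluation at the time of withdrawal will be performed with an explanation of" the reason.

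**Exposure.** The risk and benefit text of section 1 stresses that "the investigational product cannot be withdrawn after implantation". Section 9, Action taken regarding the study drug, says the same.

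**Replacement and analysis sets.** Section 4, Replacement of Withdrawn Patients, replaces patients who withdraw before discharge or Day 21 with a patient on the same treatment, up to 10 in all. Section 11, Populations for analysis, makes the FAS primary for the primary and secondary efficacy endpoints. It forms the PP set by removing FAS patients with major deviations.

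**The concern.** Withdrawal by the investigator normally serves to stop a treatment that has become unsuitable. Here the treatment is a single implantation that cannot be undone, so after surgery that purpose is gone. What remains is the end of participation, and with it the end of scheduled assessments.

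Some of the grounds can depend on how the patient is doing. An intercurrent illness that needs an interacting drug is the clearest example. Outcomes lost in this way need not be missing at random, and no SAP can recover a scan or a functional score that was never obtained.

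The rule also sits badly with the analysis sets. Section 11 expects patients with deviations to remain in the FAS, while section 4 allows their data collection to stop for any deviation.

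**Working it through.** **1. The plan's power figure, as background.** Section 11, Power & Sample size, gives 84% power for 20 patients per arm, rates of 20% and 70%, and Fisher's exact test at two-sided 5%. The exact power is the sum, over all pairs (x, y), of Bin(x; 20, 0.20) × Bin(y; 20, 0.70) wherever the Fisher p-value is at most 0.05. This gives 84.6%, so the stated figure reproduces and is not in dispute.

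If evaluable patients were lost in both arms without replacement and the rates stayed the same, power would be 83.5% at 18 per arm, 79.2% at 17, 74.0% at 16 and 68.0% at 15. Replacement can restore the count for early withdrawals. The issue is therefore selective loss of randomised patients' outcomes more than loss of power.

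**2. What a post-surgery withdrawal ends.** This sets the visits in section 7 against the endpoints in section 2.

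| Investigator withdraws the patient | Exposure ended | Outcomes no longer secured | Replaced |
|---|---|---|---|
| After surgery, before the Day 8 angiogram | None | Primary DSA, Day 14 CT, Week 12 and Week 52 | Yes |
| After the angiogram, before the Visit 4 CT | None | Day 14 CT, Week 12 and Week 52 | Yes |
| After the CT, before discharge or Day 21 | None | Week 12 and Week 52 | Yes |
| After discharge or Day 21 | None | Week 12 and Week 52, where still due | No |

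The replacement column assumes that the 10 permitted replacements are not used up.

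**3. Does the retention wording close the gap?** The sentence on completing observations is conditioned on the patient or representative deciding to withdraw, not the investigator. Even if the final evaluation is read to cover every withdrawal, it takes place when the patient leaves. An evaluation on Day 10, for example, cannot stand in for a Day 14 CT or a Week 12 score. The only explicit data rule in Populations for analysis concerns deceased patients.

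**4. Does replacement close it?** No. One withdrawal is 1/20 = 5.0% of a planned arm. With a same-arm replacement it is 1/21 = 4.8% of those randomised to that arm. The count returns to 20, but the outcome of the patient first randomised is still absent.

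**5. How many?** The documents do not say. The cap of 10 also covers consent withdrawals, so it does not estimate investigator-initiated ones.

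**The case against.** **The right is discretionary and the wording is common.** Nothing instructs investigators to stop visits because of a deviation, and section 11 expects patients with major deviations to be in the FAS. This stands, and it keeps the point minor. But the protocol states a rule that permits the loss, and the product's irreversibility makes the rule a poor fit.

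**The losses may be small.** The Week 12 and 52 outcomes are exploratory, and Week 52 goes into an addendum. CT is not among the study-specific additional measures tabulated under Risk Threshold and Degree of Distress, so a scan might exist as routine care. Adverse events ongoing at discontinuation must still be followed up. All of this is fair, but none of it secures a Day 14 CT, centrally read, for a withdrawn patient.

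**Withdrawal also protects patients**, most of whom are expected to lack capacity at entry. This stands where the ground is the patient's unwillingness or an adverse event that the patient or representative finds intolerable. The fix leaves those alone.

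**Stronger readings that the text does not support:**
- *A conflict over SAEs.* A reader might set the post-withdrawal duty to report "SAEs considered causally related to the study drug as well as any pregnancy and outcome of" the pregnancy against section 9, which requires SAEs "within 24 hours of awareness, regardless of" causality and adds: "All SAEs occurring until 30 days after study end of each patient must be reported to by the" investigator. But the section 4 sentence describes a continuing duty and does not say that only related SAEs are due. Study end in section 9 is specific to each patient. The two fit together: all SAEs until 30 days after that patient's termination, and related ones beyond that.
- *Control patients falling out of related-SAE reporting.* Staff doing safety assessments are blinded and causality is rated for every adverse event, so a control patient's SAE can be rated as related.
- *Withdrawals differing by arm.* The ICU team is blinded, and nothing in the documents shows a difference.
- *The primary angiogram being safe in any case.* An earlier DSA for suspected vasospasm replaces the scheduled one, but nothing obtains it once a patient has been withdrawn.

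**Conclusion.** The point holds as a minor fault of wording. Section 4 allows investigator-initiated withdrawal from the study after an irreversible treatment, on grounds that include any protocol deviation, without securing the outcomes still due. The primary, secondary and exploratory endpoints can all be affected, depending on when the withdrawal occurs. Each case costs the outcomes of one patient, 5% of a 20-patient arm. The number of cases and the direction of any bias are unknown, so no bias is estimated.

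The conclusion rests on two readings: that withdrawal from the study ends scheduled visits, which the study termination page supports, and that the retention sentence covers only withdrawals decided by the patient or representative. It concerns withdrawals after surgery; before implantation, a withdrawal can still prevent exposure.

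**What to change.** In section 4, Subject withdrawals, state that after clip ligation, in both arms, non-permitted medication, a protocol deviation, an intercurrent illness needing an interacting drug, or development of an exclusion criterion is recorded as a deviation or intercurrent event and does not end follow-up.

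Unless the patient or representative withdraws consent or declines further participation, scheduled visits and SAE reporting under section 9 continue. Individual procedures may be omitted for safety or distress.

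State also that these patients are not replaced and stay in the FAS, with major deviations handled through the PP set already planned in section 11.

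The cost is a protocol wording amendment, with whatever ethics and authority review it needs in the participating countries. No new visits are required, since they are already scheduled for every patient. The downside is that some patients with deviations remain in follow-up and in the primary analysis set.

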#### 487 **Replacement of Withdrawn Patients**

488 Patients that withdraw prior to hospital discharge, or day 21, whichever occurs first, will be  
489 replaced. Replacement patients will receive the same treatment as the withdrawn patient. A  
490 maximum of 10 replacements will be done.

491 Patients who die will be considered to have completed the study and will not be replaced.

492

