## 505 TREATMENT(S)

### 506 Appearance and content

#### 507 *Investigational Medicinal Product*

508 NicaPlant® is a nicardipine modified release formulation, it is presented in the form of a rod-  
509 shaped implant (2 mm x 10 mm, 4 mg nicardipine load).

510 NicaPlant® will be given on top of the standard of care-treatment as determined at the sites  
511 according to the treatment guidelines. [8]

512 A main difference to the previous study is the lack of limitations for an additional treatment  
513 with Nimodipine or any other treatment needed according the treatment guidelines since the  
514 safety of patient should not be reduced. Furthermore, the sovereignty of the study sites will  
515 not be subducted by the study since patients in emergency situations within the intensive care  
516 unit need an individual therapy adapted to their needs and with no delays.

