## 548 **Blinding and randomisation**

### 549 ***Randomisation***

550 Up to 40 patients (20 will receive standard of care, 20 will receive standard of care and 10  
551 NicaPlant® implants) will be included in the study.

552 Patients that withdraw prior to hospital dismissal will be replaced. Replacement patients will  
553 receive the same treatment as the withdrawn patient. A maximum of 10 replacements will be  
554 done. Patients who die will be considered to have completed the study and will not be  
555 replaced.

556 Patients are to be randomised at Visit 1 within 48 hrs of aneurysm rupture. A member of the  
557 study team will randomize patients in the IWRS system and will receive a randomisation  
558 code assigned to the patient. It is essential for all patients that a participation within the study  
559 is not causing any delay in the treatment and the safety and wellbeing of the patients needs to  
560 be the main focus all the time.

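### Replacement patients take the withdrawn patient's arm, so up to 10 of 50 allocations are neither random nor reliably concealed, and the withdrawals that trigger them can depend on treatment

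*Protocol*

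**What the plan says.** Two places in the protocol set the rule. Under Replacement of Withdrawn Patients: "Patients that withdraw prior to hospital discharge, or day 21, whichever occurs first, will be" replaced, "Replacement patients will receive the same treatment as the withdrawn patient", and a "maximum of 10 replacements will be done". The Randomisation text under Blinding and randomisation repeats the rule and the cap ("receive the same treatment as the withdrawn patient. A maximum of 10 replacements will be" done), but words the window differently: "Patients that withdraw prior to hospital dismissal will be replaced", with no day 21 limit. Deaths are outside the rule: "Patients who die will be considered to have completed the study and will not be replaced".

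Subject withdrawals lists the grounds on which the investigator may withdraw a patient. They include:
- a non-permitted concomitant drug;
- a protocol deviation, with no threshold given;
- an adverse event that the patient or representative finds intolerable;
- development of an exclusion criterion;
- "Intercurrent illness that necessitates pharmacological treatment with a drug which" interacts with the test treatment.

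The Concomitant Medications section bases the non-permitted list on known interactions with nicardipine. Its heading qualifies the list with the words 'unless indicated'. The Investigational Medicinal Product section says that a main difference from the previous study is "the lack of limitations for an additional treatment".

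Patients are randomised at Visit 1, within 48 hours of rupture. The operating team checks the code in the IWRS after clipping and is unblinded. The ICU team, the image reader and the outcome assessors are blinded. The responsible neurosurgeon holds IWRS access. Angiograms and CT scans are read locally for patient management as well as centrally for the endpoints.

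**The concern.** The Blinding section relies on randomisation to control selection bias. For a replacement that control is missing, because an earlier patient's arm determines the new one. If someone involved in deciding whom to enrol knows that arm, the choice of the next patient can be influenced, knowingly or not.

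The events that create a replacement are also not clearly independent of treatment. Only one arm has a test treatment for another drug to interact with, and an adverse event can be a consequence of the implant. Because the window runs to discharge or day 21, a patient can be withdrawn and replaced after the site has seen the day 8 angiogram and the day 14 CT.

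If patients who leave are at higher risk than those who take their place, and the analysis covers only those who stay, the two groups are no longer comparable. With 20 patients per arm, a few such substitutions move the estimate noticeably. Safety is also a primary objective and would be affected in the same way.

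**Working it through.** **1. The plan's own figure.** Inputs from Power & Sample size: 20 per arm, vasospasm 20% (active) and 70% (control), Fisher's exact test, two-sided 5%. Power is the sum of Bin(i; 20, 0.20) × Bin(j; 20, 0.70) over all tables (i, j) with Fisher p ≤ 0.05. Result: 84.6%, which agrees with the stated 84%.

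**2. Share of allocations not randomised.** At most 10 replacements on top of 40 patients: 10 / (40 + 10) = 20% of those enrolled. If only the 40 who were not withdrawn are analysed, the share is 10 / 40 = 25%.

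**3. Worst-case illustration.** These inputs are assumptions, not protocol figures. There is no true effect. Individual risks follow Beta(0.9, 1.1), mean 0.9 / (0.9 + 1.1) = 45%. The k highest-risk implant patients are withdrawn, replaced by k fresh draws in the same arm, and not analysed. The control arm is untouched. Simulation with 100,000 trials per row, 20 per arm, Fisher two-sided 5%:

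| k | Spurious benefit (points) | Significant in favour of implant | Significant, either direction |
|---|---|---|---|
| 0 | 0 | 1.0% | 2.1% |
| 2 | 4.5 | 2.5% | 3.0% |
| 3 | 6.3 | 3.3% | 3.7% |
| 5 | 9.2 | 5.0% | 5.2% |

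If both arms lose and replace their k highest-risk patients, the mean difference is about 0 and total rejection is about 3%. The bias comes from asymmetry between the arms.

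**4. A second mechanism, at the protocol's control rate.** Assume no true effect, p = 70% in both arms, and that each implant patient heading for an event is withdrawn, replaced and not analysed with probability w. The analysed implant event rate is p(1 − w) / [p(1 − w) + 1 − p], and the expected number of replacements is 20pw / (1 − pw).

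- w = 0.2: 0.56 / 0.86 = 65.1%; 3.3 replacements; two-sided rejection 3.3%.
- w = 0.3: 0.49 / 0.79 = 62.0%; 5.3 replacements; 4.6%.
- w = 0.4: 0.42 / 0.72 = 58.3%; 7.8 replacements; 7.1%.

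Without selective withdrawal the rejection rate is 2.5%. The direction matches step 3.

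**5. Power if additional patients are randomised afresh** (exact Fisher, 20% versus 70%, active/control):

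- 20/18: 87.8%; 18/20: 87.1%.
- Extreme case: ten outcomes lost from one arm (10 and 20 remain) and ten new patients split 5/5. At 15/25 power is 85.8%; at 25/15 it is 86.9%.
- All 50 analysed as randomised, 25/25: 94.6%.
- For contrast, ten outcomes lost with no additional patients: 68.0% at 15/15, 66.0% at 10/20, 72.7% at 20/10.

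Power can exceed 84.6% with fewer patients because Fisher's test is discrete.

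**The case against.** The strongest reply is that the rule is poor practice but no bias has been demonstrated. Four stronger readings are tempting, and the document does not support them as stated.

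- **That concealment is lost outright.** The arm is verified in theatre after clipping, the ICU team is blinded, and a central system could issue a same-arm code without telling the enrolling person. The text does not say that this person learns which arm is next. What stands is that the arm is predictable to anyone who knows the withdrawn patient's arm, and the operating team and the neurosurgeon with IWRS access can know it.
- **That the interaction grounds apply only to implanted patients.** No ground is limited to one arm, and blinded staff would have to apply them without knowing the arm. One ground may be neutral: a major complication during aneurysm repair would usually be apparent before the code is checked. What stands is that several grounds can be related to treatment.
- **That withdrawal simply deletes the outcome.** The protocol asks for a complete final evaluation at withdrawal and for follow-up of ongoing adverse events. Deaths are neither replaced nor dropped.
- **That the comparison is biased in favour of the implant.** This needs withdrawn patients to be left out of the primary analysis. The protocol makes the full analysis set primary without saying whether they remain in it, and the statistical analysis plan may settle that. The figures in steps 3 and 4 of the working rest on assumed, one-sided withdrawal.

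The conflict over other drugs is also softer than it first looks, since the words 'unless indicated' leave room for guideline treatment.

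None of this restores randomisation. Keeping every patient in the full analysis set would limit the selective loss, but the replacements' arms would still not be allocated by chance.

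**Conclusion.** The point holds. On the protocol's own wording, up to 10 of 50 enrolled patients (20%) receive an arm that is not randomised and that some site staff can predict. Withdrawal grounds that can depend on treatment, and a window that stays open after the day 8 and day 14 images are read locally, add to the risk.

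The effect on the result is possible rather than shown. If withdrawn patients are excluded and the losses are selective in the implant arm, the spurious benefit could be about 4 to 9 points, with significant results favouring the implant rising from about 1% to between 2.5% and 5%. That range is a worst case on assumed inputs. With symmetric losses, or with all randomised patients analysed with their outcomes, the exclusion bias largely disappears. The non-random allocation remains in either case, and the remedy costs little.

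**What to change.** 1. In Replacement of Withdrawn Patients and in the Randomisation text under Blinding and randomisation, replace the same-treatment sentence with: *additional patients (at most 10) are randomised with the next number on the IWRS list*. Give the window identically in both places.
2. State that all randomised patients stay in the primary analysis in the arm to which they were randomised.
3. In Subject withdrawals, state that unless consent to data collection is withdrawn, patients stay in follow-up for the day 8 DSA, the day 14 CT, safety and the week 12 and 52 outcomes. Record the deviation and use it to define the per-protocol set.
4. Reconcile the non-permitted medication list with the statement on additional treatment under Investigational Medicinal Product, as far as use of a listed drug can trigger withdrawal.

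The cost is an amendment to the wording and an IWRS setting. The statistical price is possibly unequal arms, up to about 15 versus 25 in the extreme case, where exact power (85.8 to 86.9%) is still above the stated 84%.
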